## Abstract

**Background:**

Out-of-hospital cardiac arrest is highly fatal, and the timely delivery of high-quality cardiopulmonary resuscitation (CPR) is critical for improving survival outcomes. However, current CPR training for middle school students is still mainly based on traditional teaching methods, with limited real-life scenario simulation, making it difficult to effectively enhance skill application and emergency response capacity. Manikin-based training and scenario-based drama review, as important forms of experiential learning, may offer a promising approach to optimizing CPR training models. However, high-quality evidence regarding their effectiveness in middle school populations remains limited.

**Methods:**

A single-blind cluster randomized controlled trial with a 2 × 2 factorial design will be conducted in a middle school in Hohhot, Inner Mongolia Autonomous Region. A total of 160 eligible middle school students will be recruited and randomly assigned in a 1:1:1:1 ratio to four groups: conventional CPR training group, manikin-based training group, scenario-based drama review group, and combined manikin-based training plus scenario-based drama review group. Each training session will last 90 min. The primary outcomes are CPR-related knowledge score and skill performance score. Secondary outcomes include self-efficacy (behavioral performance and evaluation), behavioral intention, course satisfaction, and skill retention rate. Data will be collected at Baseline assessment (T0), immediate post-first training assessment (T1), 3-month post-first training assessment (T2), immediate post-second training assessment (T3), 3-month post-second training follow-up (T4).

**Discussion:**

This study applies a CPR training model integrating manikin-based practice and scenario-based drama review, and systematically evaluates the independent effects and interaction effects of different intervention components using a factorial design. The expected findings will provide more practical and effective intervention strategies for CPR training among middle school students, and offer empirical evidence for optimizing school-based first aid education systems and informing relevant policy development.

**Clinical trial registration:**

https://www.chictr.org.cn, Identifier, ChiCTR2600124162.

## Introduction

1

### Background

1.1

Out-of-hospital cardiac arrest (OHCA) is a major public health concern worldwide, characterized by a relatively low incidence but a high mortality rate (1). In Europe and North America, the annual incidence of OHCA ranges from 55 to 113 cases per 100,000 population. In contrast, China reports a higher incidence of OHCA but substantially poorer outcomes, with a survival rate of only 1.6%, which is markedly lower than that reported in the United States (9%) and Europe (18%) (2). Timely and high-quality early intervention is critical for improving survival among patients with cardiac arrest (3). When effective cardiopulmonary resuscitation (CPR) and defibrillation are initiated within 4 min of cardiac arrest, survival rates can reach 49–75% (4). A growing body of evidence indicates that bystander-initiated CPR significantly improves survival outcomes in patients experiencing cardiac arrest (5).

According to data from the National Emergency Medical Services Information System (NEMSIS) in the United States, more than 23,000 individuals under the age of 18 experience OHCA each year (6). It has been suggested that at least 15% of the population needs to be trained in CPR in order to achieve a meaningful improvement in OHCA survival rates (7). Schools are widely recognized as ideal settings for delivering CPR education at a population level. The World Health Organization, through its “Kids Save Lives” initiative, recommends that all schools worldwide provide at least 2 h of CPR training annually to individuals aged 11 years and older (6). Middle school students are at a developmental stage characterized by increasing social engagement and a growing sense of responsibility. They possess strong learning and imitation abilities, making them a key target population for CPR knowledge dissemination and skill training. The school environment, as a centralized educational setting, enables the large-scale and systematic delivery of first aid training. Moreover, adolescents in this age group demonstrate high receptivity to hands-on skills and relatively strong retention, which contributes to both the effectiveness and sustainability of training outcomes. In addition, middle school students are often present at the scene of emergencies within school environments and therefore have the potential to act as “first responders.” However, their current levels of first aid knowledge and practical skills remain insufficient, increasing the likelihood of missed opportunities for timely intervention. Through a “student–family–community” dissemination pathway, combined with scenario-based and experiential learning approaches, CPR training can not only enhance students’ rescue competencies and psychological readiness but also contribute to improving overall public emergency preparedness and health literacy.

At present, cardiopulmonary resuscitation (CPR) training for middle school students is still primarily delivered through traditional methods such as lectures, demonstrations, and paper-based exercises. However, substantial limitations remain in the simulation of real-life emergency scenarios (8). Given that cardiac arrest is characterized by sudden onset, rapid progression, and an extremely limited window for optimal resuscitation, even a delay of a few seconds may adversely affect patient outcomes. As a result, conducting on-site teaching using real patients presents considerable challenges in terms of both safety and feasibility. In recent years, teaching approaches that combine manikin-based practice with scenario-based simulation have attracted increasing attention. Previous studies have demonstrated that manikin-based CPR training can significantly improve learners’ procedural skills and clinical performance, while scenario-based simulation training contributes to enhanced emergency response capability and overall performance in simulated clinical settings (5). The integration of scenario simulation and manikin practice provides learners with hands-on experiences that closely resemble real emergency environments, enabling them to engage in a continuous learning cycle of observation, reflection, and repeated practice within simulated contexts. This process not only deepens their understanding of emergency care knowledge but also improves skill proficiency and retention. However, existing studies have largely focused on medical or nursing students (9), with relatively limited research involving middle school students. Moreover, most previous studies have employed a single intervention approach, lacking systematic investigations that integrate manikin-based training with scenario-based drama review. In addition, the majority of current studies are based on non-randomized controlled designs, with insufficient analysis of the main effects and interaction effects of different teaching components, as well as a lack of follow-up assessments examining long-term skill retention. Therefore, there is a clear need to conduct rigorously designed randomized controlled trials among middle school students to systematically evaluate the effectiveness of a CPR training model that combines manikin-based practice with scenario-based drama review.

Accordingly, the present study aims to investigate the effectiveness of a CPR training approach that combines manikin-based practice with scenario-based drama review among middle school students, in comparison with conventional training methods. Through a randomized controlled trial design, this study will systematically evaluate differences in CPR knowledge acquisition, practical skill performance, and emergency response capacity across different training modalities. The findings are expected to provide a more effective intervention strategy for CPR education among middle school students and offer theoretical evidence as well as empirical support for first aid education practice and related policy development.

### Study aims

1.2

The specific objectives of this study are to: (1) compare the effectiveness of a CPR training model that combines manikin-based practice with scenario-based drama review versus conventional training methods among middle school students; (2) evaluate the impact of this intervention on CPR-related outcomes, including knowledge acquisition, skill performance, self-efficacy (behavioral performance and self-evaluation), intention to perform bystander cardiopulmonary resuscitation, and course satisfaction; and (3) assess the long-term retention of CPR skills following the implementation of the intervention.

## Methods and analysis

2

### Study design and settings

2.1

This study is designed as a single-center, single-blind, 2 × 2 factorial cluster randomized controlled trial involving middle school students aged 11–18 years. The trial will be conducted in a middle school in Hohhot, Inner Mongolia Autonomous Region. This study setting offers favorable implementation conditions and organizational advantages: cluster allocation based on existing classes aligns with routine educational management, facilitates standardized delivery of training and follow-up assessments, and effectively reduces contamination associated with individual randomization, thereby enhancing both feasibility and internal validity. The factorial design allows for the independent evaluation of the main effects of manikin-based training and scenario-based drama review, as well as their interaction effect. This study includes Baseline assessment (T0), immediate post-first training assessment (T1), 3-month post-first training assessment (T2), immediate post-second training assessment (T3), 3-month post-second training follow-up (T4), to evaluate the short-term and long-term effects of the intervention.

This study was approved by Inner Mongolia Maternal and Child Health Care Hospital Approval Form of the Medical Ethics Committee [File No (2025) Lunshen K No. (021-1)].

### Eligibility criteria

2.2

The inclusion criteria are as follows: (1) middle school students aged 11–18 years; (2) voluntary participation with informed consent obtained from both the participants and their legal guardians.

The exclusion criteria are as follows: (1) individuals with physical disabilities that limit motor activity; (2) individuals unwilling to cooperate or those who withdraw from the study during the study period.

### Recruitment and procedures

2.3

Recruitment will commence in March 2026. The study population will consist of middle school students. Prior to study implementation, permission will be obtained from school authorities. The study objectives and procedures will be introduced to students through classroom-based presentations, and informed consent forms will be distributed to both students and their legal guardians. Participants will be formally enrolled after obtaining written informed consent from their guardians and voluntary assent from the students. Following enrollment, all participants will complete a baseline assessment and will then be allocated by class to different groups through randomization, after which they will receive the corresponding interventions.

### Randomization and group allocation

2.4

This study adopts a cluster randomized design, with classes serving as the unit of randomization. The randomization process will be conducted in two stages, as follows:

#### Stage 1: selection of eligible classes

2.4.1

First, among a total of 16 classes that meet the inclusion criteria within the school, 4 target classes will be randomly selected using Microsoft Excel. The procedure is as follows: a new worksheet will be created, with Column A assigned numbers from 1 to 16 as unique identifiers for each class. In Column B, the formula = RAND() will be used to generate random numbers for each class. These random numbers will then be copied and pasted as values to prevent subsequent changes. All classes will then be sorted in ascending order based on the values in Column B, and the first 8 classes will be selected as the study sample.

#### Stage 2: random allocation to intervention groups

2.4.2

The selected 4 classes will then be randomly assigned to intervention groups using Excel. Specifically, in a new worksheet, Column A will be assigned numbers from 1 to 4 as unique identifiers for the included classes. In Column B, the = RAND() function will again be used to generate random numbers, which will subsequently be copied and pasted as values. The classes will then be sorted in ascending order based on Column B. According to the sorted order, classes will be sequentially allocated into four intervention groups: the 1st classes will be assigned to Intervention Group 1, the 2nd classes to Group 2, the 3rd classes to Group 3, and the 4th classes to Group 4. The class identifiers will remain in Column A, while the allocation will be determined by the ranking in Column B.

To ensure the validity of randomization, a single-blind design will be employed, whereby participants will be unaware of their group assignments, while only the intervention implementers will have access to the allocation information. In the event of a serious adverse event or when knowledge of group allocation is required to ensure participant safety, unblinding will be requested by the principal investigator and implemented after approval by the Ethics Committee, with the entire process fully documented. To maintain allocation concealment, the sealed envelope method will be used. Specifically, four opaque envelopes will be prepared, each labeled with a unique identifier corresponding to the class identifiers in Column A. Inside each envelope, a slip indicating the assigned group will be placed. The allocation information will remain sealed and concealed until the commencement of the intervention.

### Intervention

2.5

All participants will receive standardized conventional cardiopulmonary resuscitation (CPR) training. Based on group allocation, additional intervention components will be implemented accordingly. Training will be conducted at the class level. The training program consists of the following three components: (1) conventional CPR training: a combination of video demonstration and instructor-led explanation will be used to systematically teach the fundamental principles and procedural steps of CPR, including chest compressions, rescue breathing, and key technical considerations (the training session lasts for 60 min). (2) Manikin-based training: under instructor supervision, students will perform CPR on manikin models, focusing on essential skills such as compression depth, compression rate, hand positioning, and ventilation technique. Real-time feedback will be provided by instructors to improve procedural accuracy and standardization (the training session lasts for 60 min). (3) Scenario-based simulation (drama-based review): typical emergency scenarios (e.g., sudden cardiac arrest occurring at school, at home, or in a public park) will be constructed. Students will participate in role-playing activities (e.g., rescuer, bystander, caller for help), performing the full CPR procedure within simulated contexts while also developing emergency response, communication, and psychological coping skills. To ensure the standardization and reproducibility of the scenario-based simulation training, standardized drama scripts were developed by the research team and are provided in Supplementary material 1. The scripts were designed around a complete first-aid response sequence, including identifying an emergency, assessing the environment and calling for help, evaluating the victim’s condition, calling the emergency medical service number 120, performing standardized CPR compressions and rescue breathing, and assessing resuscitation outcomes. This structure formed a complete prehospital emergency response loop and closely integrated real-life scenarios with key professional first-aid knowledge points, thereby enhancing students’ situational engagement and practical response capacity (the training session lasts for 60 min).

All instructors were certified Basic Life Support trainers by the American Heart Association (AHA) and received standardized pre-training in CPR operational skills and teaching procedures to ensure consistency in training content, instructional materials, and performance standards. A total of eight instructors were responsible for 160 participants, corresponding to an instructor-to-participant ratio of approximately 1:20. Four CPR manikins were used for classroom demonstration and hands-on practice, and an additional two manikins were designated for skills assessment (each participant was allocated approximately 15 min per CPR skills assessment session). In total, six CPR manikins were used throughout the study.

### Study arms

2.6

All participants will receive standardized conventional CPR training. Based on random allocation, participants will then receive different forms of enhanced training or review interventions. Middle school students will be randomly assigned to one of the following four groups:

Group A (Manikin-based training + scenario-based drama review):

Phase 1: following conventional CPR video demonstration and theoretical instruction, students will undergo manikin-based CPR skills training, practicing key steps such as compression depth, rate, and rescue breathing under instructor guidance.

Phase 2: scenario-based drama review will be conducted by simulating emergency situations (e.g., sudden collapse on campus). Students will engage in role-playing (rescuer, bystander, caller for help) and complete the CPR procedure within these scenarios to reinforce skill application and emergency response capacity.

Group B (Manikin-based training only):

Phase 1: following conventional CPR video demonstration and theoretical instruction, students will receive manikin-based CPR skills training, focusing on repeated practice of compression depth, rate, and ventilation under instructor guidance. Phase 2: conventional CPR training (theoretical explanation and demonstration) will be provided.

Group C (scenario-based drama review only):

Phase 1: students will complete conventional CPR video demonstration and theoretical instruction without manikin-based practice. Phase 2: scenario-based drama review will be conducted through simulated emergency situations (e.g., sudden collapse on campus), with students participating in role-playing and completing CPR procedures to enhance practical application and emergency response skills.

Group D (control group):

Phase 1: students will complete conventional CPR video demonstration and theoretical instruction. Phase 2: conventional CPR theoretical instruction and standard procedural demonstration will be provided.

To ensure consistency across groups, all training sessions will be delivered by uniformly trained instructors. The duration and overall instructional framework will be standardized, with differences limited to the inclusion or exclusion of manikin-based training and scenario-based drama review. The detailed study flowchart is presented in Figure 1.

**Figure 1 fig1:**
[figure not shown]
Flow chart of participants recruitment and study implementation.

### Control condition

2.7

During the intervention period, the control group will receive only conventional CPR training, including theoretical instruction and procedural demonstration, without additional manikin-based practice or scenario-based drama review. The training duration will be kept consistent with that of the intervention groups to control for the potential influence of time on study outcomes.

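### Session length is 90 min in the Abstract but 60 min per component in section 2.5; if the components add up, the manikin arms get 60 extra minutes and the equal-time claim fails

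*Protocol article*

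**What the plan says.** The protocol article gives session length in two places, and they differ.

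- Abstract, Methods: "Each training session will last 90 min".
- Section 2.5 (Intervention), conventional component: "and key technical considerations (the training session lasts for 60 min". Manikin component: "Real-time feedback will be provided by instructors to improve procedural accuracy and standardization (the training session lasts for 60 min". The drama component carries the same 60-min figure.

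The text presents manikin practice as something added to conventional teaching. Section 2.5 says that everyone receives conventional training and then: "Based on group allocation, additional intervention components will be implemented accordingly". Section 2.6 (Study arms) describes Phase 1 for Group A as: "following conventional CPR video demonstration and theoretical instruction, students will undergo manikin-based CPR skills training". Group B is worded alike; Groups C and D get conventional teaching only in Phase 1. Section 2.13 (Data analysis plan) defines Factor 1 as lecture alone against lecture plus manikin practice.

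The document also commits to equal time across arms. Section 2.6: "The duration and overall instructional framework will be standardized". Section 2.7 (Control condition): "The training duration will be kept consistent with that of the intervention groups to control for the potential influence of time on study outcomes".

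**The concern.** There are two separate problems. The first is certain: 90 min per session and 60 min per component cannot both describe the same schedule. The second is conditional: if the 60-min components are delivered one after the other, as the wording of 2.5, 2.6 and 2.13 suggests, the manikin arms receive more instruction than the others in Phase 1, and the equal-time statements in 2.6 and 2.7 are false.

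Manikin training is one of only two factors in the trial, and CPR knowledge and CPR skill are both primary outcomes. The protocol itself names time as an influence to be controlled. What the manikin main effect can be said to show therefore depends on which schedule is delivered. It could be manikin practice plus extra contact time, or manikin practice in place of lecture time. The second could bear on the knowledge outcome in its own right and is not clearly the add-on contrast of 2.13.

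**Working it through.** **Inputs.** Session 90 min (Abstract). Conventional, manikin and drama components 60 min each (2.5). Phase content by arm (2.6): A is conventional then manikin in Phase 1 and drama in Phase 2; B is conventional then manikin, then conventional; C is conventional, then drama; D is conventional, then conventional. Four classes of 40 students (2.10). Four training manikins, two assessment manikins and about 15 min per student per skills assessment (2.5).

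**Can the 90 min be reproduced?** No. Whole 60-min components sum to 60, 120 or 180 min, never 90.

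**Could the other 30 min be assessment?** The text does not say so, and the figures do not fit: 40 students x 15 min / 2 manikins = 300 min per class.

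**Minutes under each reading:**

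| Reading | Phase 1, A and B | Phase 1, C and D | Phase 2, all arms | Total, A and B | Total, C and D |
|---|---|---|---|---|---|
| Components add up | 60 + 60 = 120 | 60 | 60 | 180 | 120 |
| Every session 60 min | 60 | 60 | 60 | 120 | 120 |
| Every session 90 min | 90 | 90 | 90 | 180 | 180 |

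**Time carried by each factor on the additive reading.**

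- Factor 1 (manikin), Phase 1: (120 + 120)/2 - (60 + 60)/2 = 60 min.
- Factor 2 (drama), Phase 2: (60 + 60)/2 - (60 + 60)/2 = 0 min.

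**Which statements survive each reading.**

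- Components add up: the add-on wording and the 60-min figures hold. The 90 min and both equal-time statements fail.
- Every session 60 min: time is equal. The 90 min fails, and Groups A and B cannot have a 60-min lecture and 60 min on manikins in one 60-min slot, so they get less lecture than C and D.
- Every session 90 min: time is equal. The two 60-min components still do not fit (60 + 60 = 120 > 90). A full lecture leaves 90 - 60 = 30 min for manikins in A and B, and the same 30 min has to be filled in C and D.

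No reading keeps every statement true.

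**Manikin dose.** Section 2.5 states: "Four CPR manikins were used for classroom demonstration and hands-on practice". Assume one class trains at a time, one student uses a manikin at a time, and the whole period is hands-on. Then 40/4 = 10 students share a manikin. Practice per student is 60/10 = 6 min if manikin time is 60 min, and 30/10 = 3 min if it is 30 min. These figures rest on an assumed schedule and only show that the delivered dose also depends on the answer.

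**The case against.** The strongest reply is that the only sentences about time across arms, in 2.6 and 2.7, both commit to equality. The words that suggest addition describe content and order, not minutes. Section 2.5 attaches each 60 min to a training session, so the figures can be read as session lengths by type, which leaves the arms equal. Giving the manikin arms a shorter lecture within a fixed slot is ordinary time-matching and can still be called lecture plus manikin practice. Section 2.7 also says that the control group has theory and demonstration for a matched duration, which partly answers what it does while others use the manikins. A detailed timetable is something an article may leave to the full protocol.

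Much of this is fair. The 120 v 60 gap is not established, and the absence of a timetable alone would be no finding. The hands-on minutes are illustrative and do not bear on equality between arms. But the reply does not remove the conflict between 90 and 60, which are two stated figures, not an omitted detail. Each reading that rescues equal time does so by giving up other stated durations: the 90 min and a full 60-min component in A and B, or the 60-min figures themselves. Figure 1 is not shown and may contain a schedule, but it cannot make both figures true.

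**Conclusion.** The concern holds; the durations are wrong as written. That 90 min in the Abstract conflicts with 60 min per component in 2.5 is certain. The imbalance of 60 min in Phase 1 (120 v 60, totals 180 v 120) depends on the components being additive, which is the most natural reading of 2.5, 2.6 and 2.13 but not the only one.

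On that reading the stated control for time fails for Factor 1. On the 60-min-session reading Factor 1 compares manikin practice with the lecture time it displaces. Factor 2 is balanced on the component times, assuming conventional teaching is not repeated before the Phase 2 drama; 2.6 does not say that it is. The document has no data on how extra minutes change scores, so the size and importance of any bias cannot be stated. The sample size is not affected.

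**What to change.** Add one small table of minutes by arm and phase, and make the Abstract, 2.5, 2.6 and 2.7 agree with it. Then do one of the following.

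1. Keep equal time. Set the same Phase 1 length in all four arms, state what Groups C and D do during the manikin period, and correct the 90 min or the 60-min figures to match. If lecture is shortened in A and B, say so, and describe Factor 1 accordingly.
2. Keep the additive schedule. Delete the time-control claim from 2.6 and 2.7, and interpret Factor 1 as manikin practice together with its extra contact time.

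If sessions have already begun, record and report the minutes delivered in each arm. The cost is protocol wording and the table; sample size, outcomes and model stay as they are.
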